## Abstract

**Introduction::**

As a major public health problem, depression has a negative impact on individuals and society. The aim of this well-designed trial is to evaluate the efficacy and safety of electroacupuncture (EA) treatment for depression.

**Methods/Design::**

A 3-arm parallel, nonblinded, randomized controlled trial will be performed in 4 hospitals (centers). A total of 144 participants will be divided into 3 groups: EA group, manual acupuncture (MA) group, and western medicine group. Participants in EA group and MA group will receive 12 sessions of acupuncture treatment for 4 weeks. Participants allocated to western medicine group will only take 20 mg fluoxetine orally per day for 4 weeks. The primary outcome is Hamilton Depression Scale. Secondary outcomes are Self-Rating Depression Scale, Depression Scale of traditional Chinese medicine (Depression Scale of Traditional Chinese Medicine), brain fMRI and blood biomarkers including neurotransmitters serotonin, dopamine, noradrenaline, inflammatory cytokines inerleukin (IL)-1β, tumor necrosis factor-α, IL-6, and neurotrophin BDNF. All the outcomes will be assessed at baseline, 4 weeks after EA treatment onset and 6-month follow-up.

**Discussion::**

The results of this trial will verify the efficacy and safety of EA treatment for depressive patients and provide acupuncturists and clinicians with robust clinical evidence.

**Trial registration::**

Chinese Clinical Trial Registry identifier: ChiCTR1900023420. Version 1. Registered on 26 May 2019. http://www.chictr.org.cn/edit.aspx?pid=37621&htm=4

## Introduction

1

Characterized by emotional, behavioural, and cognitive features, symptoms of depression include dysphoric mood, feelings of hopelessness, loss of interest, social withdrawal, eating disorder, insomnia, fatigue, low self-esteem, and poor concentration. As a major public health problem, depression has a negative impact on individuals and society. A recent meta-analysis^[1]^ benchmarking the prevalence of depression in the community from 30 countries between 1994 and 2014 reported that the 1-year and lifetime prevalence of depression was 7.2% and 10.8%, respectively. Depression is associated with impaired physical or mental function^[2]^ and a substantial role loss in social life.^[3]^ It was found to have a worse impact on quality of life when compared with chronic diseases such as hypertension or diabetes.^[4]^ Furthermore, health services for depressed patients will bring about considerable financial costs.^[5]^

In most cases, depressed patients are treated with antidepressants^[6]^ such as citalopram, escitalopram, nortriptyline, milnacipran, mirtazapine, piracetam, and fluoxetine. Whereas, antidepressants have many side effects such as nausea, fatigue, insomnia, dry month, blurred vision, constipation, sexual problems.^[7]^ It was reported that Australians and Americans with depression had a preference for complementary therapies.^[8–10]^ Based on the theory of Traditional Chinese Medicine (TCM), acupuncture has a long history of use. Since that electroacupuncture (EA) was reported to effectively reduce depressive behaviors with few side effects,^[11]^ studies have found that EA can regulate neurotransmitter levels of serotonin (5-HT), noradrenaline (NE), and dopamine (DA) in animal models of depression.^[12]^ EA has been verified to trigger functional magnetic resonance imaging (fMRI) changes in the default mode network, anterior cingulate cortex, and amygdala-hippocampal formation^[13,14]^ where dysfunction has been previously detected in depressive disorders.^[15]^ Inflammatory cytokines including interleukin (IL)-1β, tumor necrosis factor (TNF)-α, and IL-6 were found to be changed in patients with depression treated by EA^[16]^ which was also capable of affecting neurotrophin levels of brain derived neurotrophic factor (BDNF) in depressed rats.^[17]^

However, a recent Cochrane meta-analysis^[18]^ focusing on the effectiveness of acupuncture or EA treatment for depression revealed that acupuncture or EA's effect compared with medication in reducing depression severity was unclear owing to the very low quality of evidence. Considering most trials did not report adverse events (AE), the risk of AEs with acupuncture or EA was also uncertain. Besides, few studies included follow-up assessment. Thus, a high-quality randomized controlled trial (RCT) is urgently needed. This protocol has been designed to conduct a multicentered, randomized controlled trial to assess the clinical efficacy and safety of EA for depression.

## Methods/Design

2

### Study design

2.1

According with the Consolidated Standards of Reporting Trials^[19]^ and Standards for Reporting Interventions in Clinical Trials of Acupuncture guidelines for acupuncture studies,^[20]^ a multicentered, parallel, randomized controlled trial will be conducted from June 2019 to June 2021 (Fig. 1). Figure 2 indicates the study schedule for enrollment, treatments, outcome measurements, and data collection. The SPIRIT checklist can be found in Additional file 1.

**Figure 1 F1:**
[figure not shown]
The planned flowchart of the trial.

**Figure 2 F2:**
[figure not shown]
The study schedule for enrollment, treatments, outcome measurements and data collection. HAMD = Hamilton Depression Scale, SDS = Self-rating Depression Scale.

### Participants

2.2

#### Patient screening

2.2.1

To conduct the safety assessment of patients and exclude patients with fatal conditions such as renal failure, heart failure, hepatic impairment, patient screening will be done by an independent researcher. It will depend on history inquiry, history recording, and laboratory tests which include complete blood count, urine analysis, fecal analysis, electrocardiograph, function of kidney, liver, and thyroid.

#### Inclusion criteria

2.2.2

Patients who meet the following criteria will be enrolled in the trial: meet the diagnostic criteria of depression according to the Diagnostic and Statistical Manual of Mental Disorders, Fifth Edition^[21]^; aged 18∼75 years old, males or females; scores of Hamilton Depression Scale 17 (HAMD-17) are >17; able to understanding and answering the questions of scales; did not receive acupuncture treatment in the past month; willing to sign informed consents.

#### Exclusion criteria

2.2.3

Patients who meet any of the following criteria will be excluded from the trial: undergoing other anti-depressive treatments within 1 month; history of personality disturbance, psychiatric disorders or brain diseases; complications of severe heart failure, infectious diseases or immune deficiency; having suicide thoughts; history of claustrophobia; having metal in their bodies; unable or unwilling to finish the whole trial.

#### Elimination criteria

2.2.4

Data from patients who meet any of the following criteria after treatment will be eliminated from the analyses of this trial: occurrence of severe AEs; aggravation of depression severity; poor compliance.

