#### Primary outcome

2.5.1

The primary outcome of the clinical study will be the score changes of Hamilton Depression Scale (HAMD) between baseline, 4 weeks after EA treatment onset, and 6-month follow-up.

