### Safety assessment

2.6

During the whole treatment, participants safety will be assessed to avoid adverse events (AEs). AEs of acupuncture mainly include local bleeding or pain, local redness or bruising, itching, and dizziness, whereas fluoxetine will bring about a series of AEs such as nausea, upset stomach, constipation, headaches, insomnia. A researcher will record the time of occurrence, severity, progress and treatment of AEs at each visit. Once any severe AE occurs, both the principal investigator and the institutional review board (IRB) will be informed and take prompt actions simultaneously.

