### Statistical analysis

2.9

SPSS 24.0 (SPSS Inc., Chicago, IL) will be used to conduct the whole data analysis. The intention-to-treat (ITT) analysis will include any participant who has at least one treatment session. The “last observation carried forward” rule will be applied to manage missing data in ITT analysis of secondary outcomes, whereas the maximum likelihood estimation method will be used for primary outcome. Any participant who receives at least 9 treatment sessions during the trial will be included in per protocol analysis.

Considering the homogeneity of the baseline characteristics between groups, group *t* test for quantitative data and Chi test for qualitative data will be applied. Group *t* test for normally distributed data or Mann-Whitney *U* test for non-normally distributed data will be used to compare variables between groups. For differences within each group, repeated measured analysis of variance will be used to analyze assessments of different time points, whereas Wilcoxon signed-rank test will be selected for non-normally distributed data. A *P* value <.05 will be considered statistically significant (2-sided).

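### Section 2.2.4 removes patients with severe AEs, worsening depression or poor compliance from the analyses, section 2.9 keeps them in the ITT analysis, and nothing says which rule prevails

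*Protocol article*

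**What the plan says.** Section 2.2.4 (Elimination criteria) applies after treatment has begun. It opens with "Data from patients who meet any of the following criteria after treatment" and continues that these data "will be eliminated from the analyses of this trial: occurrence of severe AEs; aggravation of depression severity; poor compliance". The rule is not restricted to a per-protocol set or to efficacy.

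Section 2.9 (Statistical analysis) defines two analysis sets, neither of which refers to 2.2.4:

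- "The intention-to-treat (ITT) analysis will include any participant who has at least one treatment session".
- "Any participant who receives at least 9 treatment sessions during the trial will be included in per protocol analysis".

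The same section handles missing primary-outcome data by maximum likelihood.

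Four other places bear on the point:

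- Section 2.5.1 makes change in HAMD score the primary outcome.
- The Introduction states the purpose as "to assess the clinical efficacy and safety of EA for depression".
- Section 2.6 (Safety assessment) says "A researcher will record the time of occurrence, severity, progress and treatment of AEs at each visit", and has severe AEs reported to the principal investigator and the IRB. Section 2.8 adds an adverse events form and monthly DSMB monitoring.
- Section 2.3 says that the study is not blinded.

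**The concern.** Two of the three elimination criteria are results of the trial. Worsening depression is the unfavourable end of what the HAMD measures, and a severe AE is a central safety result. The third, poor compliance, is not an outcome. It is a post-randomisation event that 2.2.4 does not define, and it would be judged by people who know the treatment.

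Removing patients on such grounds gives up the protection of randomisation. Each arm is then described by the patients who did not do badly on it. A severe AE that leads to removal cannot be counted in a comparison of severe AEs.

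Because 2.9 says something different, the primary analysis is also not fixed. An unblinded team could settle which rule applies after outcomes are known. The Abstract nevertheless promises that "The results of this trial will verify the efficacy and safety of EA treatment for depressive patients".

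**Working it through.** **Step 1: the two sections side by side.** Take a participant who has at least one session.

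| Participant | Section 2.2.4 | ITT, section 2.9 | Per protocol, section 2.9 |
|---|---|---|---|
| Worsens, at least 9 sessions | out | in | in |
| Severe AE, at least 9 sessions | out | in | in |
| Poor compliance, fewer than 9 sessions | out | in | out |

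The elimination rule matches neither set. It agrees with the per-protocol set only on compliance, which the session count already covers. No sentence says which section governs.

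**Step 2: what following 2.2.4 would do to HAMD change.** The article gives no HAMD means or SDs and no threshold for aggravation, so every input here is an assumption. Let the change X be normal with mean μ and SD σ (negative is improvement), and delete everyone with X above a cut-off c. With b = (c − μ)/σ:

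- share deleted = 1 − Φ(b)
- mean of those kept = μ − σ·φ(b)/Φ(b)

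For μ = -8, σ = 7, c = 0: b = 8/7 = 1.143, Φ(b) = 0.8735 and φ(b) = 0.2076. The share deleted is 12.7%, and the mean kept is -8 − 7 × 0.2076/0.8735 = -9.7.

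For μ = -5, σ = 7, c = 0: b = 5/7 = 0.714, Φ(b) = 0.7625 and φ(b) = 0.3091. The share deleted is 23.8%, and the mean kept is -5 − 7 × 0.3091/0.7625 = -7.8.

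The true difference is -8 − (-5) = -3.0. After deletion it is -1.8 (-9.66 + 7.84).

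**Step 3: dependence on the cut-off** (same means, SD 7).

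| Deleted if HAMD rises by more than | Share deleted, two arms | Difference left (true 3.0) |
|---|---|---|
| 0 points | 12.7% and 23.8% | 1.8 |
| 3 points | 5.8% and 12.7% | 2.2 |
| 5 points | 3.2% and 7.7% | 2.4 |

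**Step 4: dependence on the other assumptions** (cut-off 0).

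- Means -8 and -5, SD 6: 9% and 20% deleted; 3.0 becomes 2.0.
- Means -10 and -7, SD 6: 3.0 becomes 2.2.
- Equal means of -8, SDs 6 and 8: kept means are -9.1 and -10.3, a spurious difference of 1.2 where the true one is 0.
- Identical distributions (mean -8, SD 6 in both arms): the between-arm difference stays 0, but both arms show -9.1 instead of -8.

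Deleting worseners therefore inflates improvement within every arm. The between-arm effect can be a shrunken difference, a spurious one, or none. Deletions for severe AEs or poor compliance are not modelled.

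**Step 5: safety.** In any analysis that applies 2.2.4 literally, the severe-AE rate is 0% in every arm whatever the true rate, because having such an event is the ground for removal.

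**The case against.** The strongest reply is that 2.9 already plans a sound primary analysis: an ITT set, likelihood-based handling of missing HAMD data and a separate per-protocol set. If 2.9 governs, these patients stay in and the efficacy bias does not arise. This stands as far as it goes. A reader might infer that the efficacy and safety results are bound to be selected on outcome and that the trial cannot meet its aim. The article does not support that, because it never says that 2.2.4 overrides 2.9. Equally, it never says the reverse.

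A reader might also infer that severe AEs vanish from the trial. They do not. Sections 2.6 and 2.8 have them recorded, reported and monitored. What is missing is any statement that eliminated patients remain in the safety analysis.

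Nor can it be asserted that the arms would lose patients in different proportions, or that the contrast between them is certainly biased. The article gives no rate of worsening, severe AEs or poor compliance by arm.

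The 3.0-to-1.8 figure depends on counting any HAMD rise as aggravation, the harshest of the three cut-offs shown.

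Two further defences are weaker. One is that 2.2.4 was meant for the per-protocol set, but its wording does not say so and the per-protocol definition mentions neither severe AEs nor worsening. The other is that an article condenses the full protocol. That explains missing detail, but not two explicit rules that conflict.

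**Conclusion.** The point holds as an unresolved contradiction between 2.2.4 and 2.9, with serious consequences if 2.2.4 is the rule applied. It must be fixed, because it concerns which patients enter the primary analysis and the safety comparison.

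Two consequences follow from the wording of 2.2.4 alone: deleting patients who worsen overstates within-arm improvement, and severe AEs leave any analysed comparison. A biased between-arm difference is possible, but its direction and size are unknown.

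Under the assumed normal changes of -8 and -5 with SD 7, a true 3.0-point difference would be reported as 1.8 to 2.4 points, depending on the cut-off for worsening. These figures show scale only and do not predict this trial's result.

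**What to change.** Remove 2.2.4 as an analysis rule and bring it into line with 2.9:

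- Patients with a severe AE, worsening or poor compliance stay in the ITT efficacy analysis, with worsening counted as part of the HAMD result.
- All treated patients stay in the safety analysis, with severe AEs counted by arm.
- Compliance is used only to define the per-protocol set.

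This concerns analysis sets only and leaves clinical management untouched.

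The cost is wording. Compared with an analysis that follows 2.2.4, within-arm improvement may look smaller, and the between-arm contrast could move either way. In the -8 and -5 illustration it would be larger.

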### Quality control

2.10

To ensure the quality of this trial, supervisors from clinical evaluation center of Shanghai Shuguang Hospital will be responsible for the monitoring of case report forms, participants’ compliance with EA treatments, trial master file, serious AEs records, and data set regularly and strictly based on the quality standard of good clinical practice.

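### Section 2.2.4 drops patients with severe AEs, worsening depression or poor compliance from the trial's analyses without limit, which contradicts the ITT and per protocol sets in 2.9

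*Protocol article*

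**What the plan says.** Protocol article, 2.2.4 (Elimination criteria): data from patients who meet any of three criteria after treatment "will be eliminated from the analyses of this trial: occurrence of severe AEs; aggravation of depression severity; poor compliance". No analysis set is named and no exception is made.

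Protocol article, 2.9 (Statistical analysis): "The intention-to-treat (ITT) analysis will include any participant who has at least one treatment session". For the other set: "Any participant who receives at least 9 treatment sessions during the trial will be included in per protocol analysis". Neither sentence refers to 2.2.4. The same section uses maximum likelihood for missing primary-outcome data and last observation carried forward for secondary outcomes.

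Protocol article, 2.5.1 (Primary outcome): the primary outcome is the "score changes of Hamilton Depression Scale (HAMD) between baseline, 4 weeks after EA treatment onset, and 6-month follow-up". Section 2.3 states that the trial is not blinded.

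On safety, the Introduction notes of earlier evidence: "Considering most trials did not report adverse events (AE), the risk of AEs with acupuncture or EA was also uncertain". It gives the purpose of this trial as "to assess the clinical efficacy and safety of EA for depression". Section 2.6 has AEs recorded at each visit and adds: "Once any severe AE occurs, both the principal investigator and the institutional review board (IRB) will be informed".

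**The concern.** The elimination rule acts after randomisation and on what happened to the patient under treatment. Three things are at stake.

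- **The analysis population is not fixed.** A treated patient who gets worse belongs to the ITT analysis under 2.9 and to no analysis under 2.2.4. With two opposite instructions in force, the choice could be made after the data are seen.
- **One criterion is the outcome itself.** Worsening depression is a poor result on HAMD change. Removing such patients makes every arm look better than it was and alters the comparison between arms. Section 2.2.4 gives no threshold for worsening or for poor compliance, and whoever applies it knows the treatment arm.
- **Safety is a stated aim.** The protocol justifies the trial partly by poor AE reporting in earlier trials. Under 2.2.4 as written, the patients with the worst AEs would be missing from the analysed comparison.

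**Working it through.** **Step 1. The sections side by side.** The contradiction is textual and needs no numbers.

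| Patient | ITT under 2.9 | Per protocol under 2.9 | Under 2.2.4 |
|---|---|---|---|
| 12 sessions, severe AE | in | in | out |
| 12 sessions, depression worse | in | in | out |
| 5 sessions, counted as poor compliance | in | out | out |

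Section 2.2.4 agrees with the per protocol definition only in the last row, and only if poor compliance means fewer than 9 sessions, which it does not say. It disagrees with the ITT definition in all three rows.

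**Step 2. Effect on efficacy (illustration).** The plan has no figure to reproduce, and the article gives no HAMD mean or SD. The inputs are assumptions: improvement is normal with mean m and standard deviation s, and worsening means any rise in HAMD from baseline. Let z = m/s.

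- Share removed = 1 − Φ(z)
- Mean improvement of those left = m + s·φ(z)/Φ(z)

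Example with s = 5:

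- m = 10, z = 2.0: removed 1 − 0.9772 = 2.3%; mean 10 + 5 × 0.0540/0.9772 = 10.28.
- m = 8, z = 1.6: removed 1 − 0.9452 = 5.5%; mean 8 + 5 × 0.1109/0.9452 = 8.59.
- Difference 10.28 − 8.59 = 1.69, against a true 2.0.

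Across the assumed SDs, true means 10 and 8:

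| s | Removed, better arm | Removed, worse arm | Mean left, better | Mean left, worse | Difference |
|---|---|---|---|---|---|
| 5 | 2.3% | 5.5% | 10.28 | 8.59 | 1.69 |
| 6 | 4.8% | 9.1% | 10.63 | 9.08 | 1.54 |
| 7 | 7.7% | 12.7% | 11.09 | 9.66 | 1.43 |
| 8 | 10.6% | 15.9% | 11.63 | 10.30 | 1.33 |

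Improvement is overstated by 0.3 to 1.6 points in the better arm and by 0.6 to 2.3 in the worse arm. A second set of assumed means, 8 and 5, gives the same pattern: for s = 6, 7 and 8 the true 3.0-point difference becomes 2.0, 1.8 and 1.7. If two arms have the same distribution (8 and 8, s = 7), both means rise from 8 to 9.66 and the difference stays at 0.

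**Step 3. Effect on the safety analysis.** If every patient with a severe AE is removed, the analysed count is zero in each arm by construction. Hidden rate = k/N, with assumed event counts k. Arm size is taken both as 144/3 = 48 and as the 36 per group stated in 2.7.

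| k | N = 48 | N = 36 |
|---|---|---|
| 1 | 2.1% | 2.8% |
| 2 | 4.2% | 5.6% |
| 3 | 6.3% | 8.3% |
| 4 | 8.3% | 11.1% |

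Each of these would be analysed as 0%.

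**The case against.** The best defence is that 2.9 is where analysis sets are defined, that its ITT sentence is unqualified, and that 2.2.4 sits under Participants and reads like a list of per protocol exclusions. The sponsor may well have meant it so. This stands as a guess about intent, and it makes the consequences conditional: nobody can say from the document that patients would in fact leave the ITT analysis. It does not remove the conflict. Section 2.2.4 speaks of the trial's analyses in general, and 2.9 gives the per protocol set its own criterion, which a patient with 12 sessions and a severe AE meets. Even if that was the intent, the text has to be changed to say so.

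A second objection is that AEs are not lost. This is right as to collection: 2.6 records them at each visit and escalates severe ones, 2.8 provides monthly monitoring by the DSMB, and 2.10 has the records checked. A reader might infer that the plan conceals harms; the document does not support that. The loss, on the literal reading, is in the analysed comparison. Section 2.9 also names no safety set, so this limb rests on the unlimited wording of 2.2.4.

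Third, the numbers in the illustration are assumed, and counting any rise as worsening is the broadest reading. A threshold for clinically relevant worsening would remove fewer patients. This stands, and the figures show direction and order of size only.

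**Conclusion.** Wrong as written. Section 2.2.4 contradicts both analysis sets in 2.9, and no other section resolves it. This part rests on the text alone.

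Followed literally, the rule inflates improvement within arms, distorts the contrast between arms that differ, and takes patients with severe AEs out of the analysed safety data. The sizes (0.3 to 2.3 points within an arm, a 2.0-point difference cut to between 1.7 and 1.3) depend on normal changes, assumed means and SDs, and worsening read as any rise.

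A reader might infer that the rule favours electroacupuncture. The documents do not support this: in the illustration the difference shrinks, two identical arms show no bias in their difference, and nothing indicates which arm would have more worsening. Nor should the mention of severe AEs in 2.6 and of serious AE records in 2.10 be read as a gap in reporting; it is probably one concept under two words.

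The correction should be made, but it is a repair of wording and not of the design.

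**What to change.** Replace 2.2.4 with:

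> *Severe AEs or aggravation of depression may lead to stopping study treatment, but all participants who start treatment stay in the ITT analysis and in the AE summary by arm. Poor compliance, meaning fewer than 9 treatment sessions as in 2.9, removes a participant from the per protocol analysis only.*

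This makes 2.2.4 agree with both definitions in 2.9 and gives poor compliance a threshold. The threshold for worsening no longer affects who is analysed.

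The cost is one text amendment, with no new visit, scale or patient. AE collection stays as 2.6 has it, during treatment; extending it to the 6-month visit would be a separate change with its own cost and is not needed here. Sections 2.6 and 2.10 need no edit for this point. The wording does not settle how a count of sessions applies to the fluoxetine arm, which is a separate question about 2.9.
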